### 3.9. Intervention

This intervention will start soon after birth, once the inclusion criteria are met, and will continue over 2 weeks during hospitalisation, minimising the effect of mother–infant separation in the NICU. In any case, participants will be excluded if they reach the inclusion criteria at more than 36 weeks of GA at test, thus when it’s presumed that they will not complete the two weeks of intervention. 

The EVC will take place in the hospital room while infants are in their individual incubators or open cribs. In the intervention group, mothers will be asked to speak and sing to their infants continuously over a 10 min period for each type of intervention (20 min in total). Mothers will be asked to talk in their native language and to sing familiar songs, while observing their infant’s reactions. The order of the two vocalisations, speaking and singing, will be reversed in the next intervention.

EVC will be performed by mothers three times per week for 2 weeks, more than 1 h after afternoon feeding. It will begin when the newborns are in an active sleep state, in calm awake state or in active awake state, but not in deep sleep or crying. 

The intervention will not begin during deep sleep state, in order to protect the infant sleep cycles and his stability [27]. The calm awake state is the most suitable for beginning early sensory interventions and interaction with the family, in stable preterm infants [70]. However, there is the need not to overwhelm the infant in this precious attentional state, where the brain expects sensory experience to grow and mature [20].

Preterm infants will be enrolled from 25 + 0 to 32 + 6 weeks of GA, following the established inclusion criteria.

Two fixed cameras will record the facial and upper torso movements of the mothers and infants. Mothers will be free to choose the content and style of their speech and singing, but will be asked to refrain from touching the infant, while maintaining eye contact with them. They will be told to place their face in front of the incubator opening so as to be as close as possible to the infant’s head. 

To improve adherence to the intervention protocol, concomitant medical procedures will not be permitted during the intervention. 

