### 3.3. Participants

Eighty preterm infants, born at 25–32 weeks and 6 days GA, will be recruited from the four centres (20 per centre). Recruitment will be undertaken in each centre by a trained research assistant (RA), who will review birth records daily. After obtaining permission from the attending physicians of both the mother and infant, the RA will invite qualifying families to participate and will obtain written informed consent from those enrolling. Infants will be then assigned to the EVC intervention or control group using a randomised design, stratifying infants by gender and GA (see Randomisation). Mothers whose infants are assigned to the control group will be asked to spend the same amount of time as that of mothers in the intervention group, observing their infants’ spontaneous behaviour, with the subsequent compilation of an observation grid developed ad hoc, according to few indicators drawn from The Neonatal Behavioural Assessment Scale. The mothers whose infants are assigned to the control group will be asked not to vocally interact with them during the observational intervention.

Recording sessions will take place midway between the feeding cycles, more than 1 h after the feed and more than 4 h after the last medical exam.

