### 3.6. Exclusion Criteria

The exclusion criteria for the newborns will be: PVL grade III and IV, IVH grade III and IV, sepsis (vertical and horizontal), congenital malformations and/or genetic abnormalities, requiring respiratory support with high flow/nCPAP repeated apnoea associated with bradycardia and fall of saturation, hyaline membrane disease, respiratory distress syndrome, and hyperbilirubinaemia requiring exchange transfusions during hospitalisation. 

Lack of informed consent will exclude the infant from the study.

The exclusion criteria for the mothers will be presence of depressive symptoms, drug abuse, and age below 18 years.

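### As worded, the protocol permits infants to be excluded after randomisation: the order of the 36-week rule and assignment is ambiguous, and some exclusion events have no cut-off at assignment

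*Protocol article*

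**What the plan says.** Section 3.3 gives the sequence at entry. Birth records are reviewed daily and permission is obtained from the attending physicians. Then "the RA will invite qualifying families to participate and will obtain written informed consent from those enrolling", after which "Infants will be then assigned to the EVC intervention or control group using a randomised design". No waiting step between consent and assignment is named.

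Section 3.9 ties the first session to readiness: "This intervention will start soon after birth, once the inclusion criteria are met". It adds that "participants will be excluded if they reach the inclusion criteria at more than 36 weeks of GA at test", for the reason given as "thus when it’s presumed that they will not complete the two weeks of intervention".

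The exclusion list in section 3.6 includes "sepsis (vertical and horizontal" forms, and "hyperbilirubinaemia requiring exchange transfusions during hospitalisation". It also names respiratory support and repeated apnoea with bradycardia and desaturation. None of these carries a time limit tied to assignment.

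Under section 3.8 the centre investigator registers the infant in the web system and receives the arm; the sequence itself is concealed. Section 6 says that participants cannot be blinded. It blinds physiological analysts, video coders and the administration of cognitive and linguistic tests.

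**The concern.** Randomisation protects the comparison only if the set of infants analysed is fixed without regard to the arm. Here a person applying the text at the bedside could assign an infant, start sessions and then exclude it because sepsis or an exchange transfusion occurs in the second week. The same person could assign an infant at consent and drop it later for not being ready by 36 weeks.

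If that happened, the decision might be taken by someone who knows the allocation, since no blinded role is named for eligibility. For one criterion there is a second route to bias. Section 1.4 reports that EVC lowers critical events such as apnoea and bradycardia, and section 3.6 excludes for repeated apnoea with bradycardia. Applied once sessions have begun, that exclusion would select on something the intervention may alter. Removal at this stage would affect the primary HRV comparison as well as the later outcomes.

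**Working it through.** The point turns on the order of events, so the check is to set the passages side by side.

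**1. When is the arm assigned?** Section 3.3: after consent, with no later trigger stated. Section 3.8: through web registration by the centre investigator, who then knows the arm.

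**2. When can the 36-week rule act?** Infants are born between 25+0 and 32+6 weeks (section 3.5). Taking 36 weeks as 36+0:
- born at 32+6: 36+0 minus 32+6 = 3 weeks 1 day = 22 days after birth;
- born at 25+0: 36 minus 25 = 11 weeks = 77 days after birth.

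The rule therefore first applies more than 22 days after birth. It presumes a wait that section 3.3 does not describe. Whether the wait falls before or after assignment is not stated.

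**3. Does the rule point to the right list?** It speaks of reaching the inclusion criteria. Most of section 3.5 is fixed at or near birth: gestational age, 10-minute Apgar, birth weight and birth head circumference. An infant cannot come to meet these weeks later. What mainly changes with time is in section 3.6 (respiratory support, repeated apnoea). The trigger is thus loosely drawn as well as loosely timed.

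**4. Can the section 3.6 events be known at assignment?**

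| Criterion | Can it first occur after assignment? | Cut-off stated? |
|---|---|---|
| Exchange transfusion, over the hospital stay | Yes | No |
| Horizontal sepsis | Yes | No |
| Repeated apnoea with bradycardia | Yes | No |

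Sessions start soon after birth and run for two weeks in hospital. A screen of birth records cannot show what happens in that fortnight.

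**5. Is there a figure to check?** Only the sample size in section 3.7, for scale. For HF power the difference is 17 − 15 = 2 and the SD is √((2.6² + 2.4²)/2) = 2.50. With two-sided alpha 0.025 (sidedness is not stated) and power 0.80 (the article labels it beta), n = 2 × (2.50 × (2.241 + 0.842)/2)² = 29.75, or 30 per group against the stated 29. That is close enough to count as reproduced. Enrolling 40 per group tolerates 1 − 29/40 = 27.5% loss before falling to 29. After the planned 20% loss, 40 × 0.80 = 32 per group remain, with HF power 0.83. The section does not say whether its 20% includes exclusions of the kind discussed here. These figures neither support nor refute the point. The issue is which infants are removed, more than how many.

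**The case against.** The strongest reply is that eligibility is meant to come first. Section 3.3 has the research assistant invite families who already qualify, the Abstract describes stable infants being enrolled and randomised, and section 3.9 itself says that enrolment follows the inclusion criteria. On that reading the 36-week sentence is an upper limit on entry, its stated reason looks forward, and the concealed sequence protects the decision. Section 3.6 is also an ordinary eligibility list. Where the authors intend later removal from analysis they say so, as for the neurological and audiological results in section 5.2.1, which are a separate matter. Finally, Figure 1 may show the order but is not reproduced in the text at hand, and an article condenses a fuller protocol.

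Much of this stands. A reader might infer that eligibility is in fact settled after randomisation by staff who know the arm. The document does not support that: it does not say when the exclusions are applied or by whom. Nor could EVC itself influence a readiness decision, because sessions begin only once the criteria are met. At most, such a decision could be coloured by knowledge of the arm.

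The reply does not dispose of the open window. A check on qualifying families at consent cannot settle a criterion worded to cover the hospitalisation. Reading that as the stay up to entry is possible, but the text does not say so.

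**Conclusion.** The point holds in a limited form. The stated rules permit an infant to be excluded after it has been randomised. For the 36-week rule the order is ambiguous. For exchange transfusion and horizontal sepsis the missing cut-off at assignment is plain on the page.

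It would go too far to say that the randomised comparison is already broken. That needs the exclusions to be applied after assignment, and in a way that differs by arm; the document shows neither. The size of any bias cannot be computed from it, and no rate of such exclusions is given from which to estimate a loss of power.

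The conclusion rests on a literal reading of sections 3.3, 3.6 and 3.9 together. If Figure 1 or the full protocol confirms eligibility before web assignment and keeps assigned infants in the analysis, only the article's wording needs correcting. This is a worthwhile and nearly free correction, not a fatal flaw.

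**What to change.** Reconcile sections 3.3, 3.6 and 3.9 as follows.

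- State that all of 3.5 and 3.6, together with the existing 36-week limit, are confirmed once, immediately before the web assignment.
- Limit the 3.6 exclusions to events that have occurred up to that moment, so that the hospitalisation wording no longer leaves the window open.
- Reword the 36-week sentence so that such infants are not randomised, in place of participants being excluded.
- State that every assigned infant stays in its randomised group for analysis, whatever 3.6-type event occurs later.

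The clinical handling of an infant after such an event is outside this point and need not change. The cost is protocol wording and the timing of web registration. Some consented infants will never be randomised, and infants with later events will add some noise to the HRV and developmental outcomes.

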## 2. Hypothesis

We hypothesise that EVC can enrich the preterm infants’ sensory and interactional experience and that this mother-driven environmental enrichment impacts the infant’s physiology by enhancing cardiorespiratory maturation and autonomic regulation that persist during interventions and possibly heart rate variability (HRV). 

HRV is representative of the functional state of an infant’s autonomic nervous system (ANS). ANS maturation is accompanied by increasing HRV with a concomitant augmentation of parasympathetic activity. A preterm infant’s GA correlates with HRV; preterm infants demonstrate lower HRV parameters than term infants [57]. Early interventions aimed at involving parents in engaging with preterm infants have shown important effects on an infant’s HRV [58] and respiratory sinus arrhythmia [59], the two indices of autonomic regulation and maturation of the ANS. 

We also hypothesise that an interactive and relational-based enriched auditory environment can impact an infant’s neurobehavioral development, as evidenced by the General Movements score (for details, see Secondary Outcome Measures).

Specific interventions directed at improving early care in the NICU, such as the Newborn Developmental Care and Assessment Program [60], skin-to-skin care [61], and massage therapy [61,62], have shown significant effects on neurodevelopmental outcomes. Research suggests that early interventions aimed at reducing the sequelae of prematurity can have positive effects, especially in the short-term periods [63,64]. However, many interventions lack long-term assessments, particularly on the infants’ neural and behavioural development [65].

Thirdly, in a long-term prospective design, we will test if earlier and regular exposure to salient linguistic stimuli in interactive contexts will impact preterm infant development, particularly the cognitive and linguistic performance, at 6, 12, and 24 months CA. Adult language input is important for healthy language development and preterm infants are at risk for long-lasting language delays [66,67]. Thus, we expect to find a direct effect of the intervention on the aforementioned developmental domains.

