### 3.5. Inclusion Criteria

The inclusion criteria for the newborns will be: GA between 25 + 0 and 32 + 6 weeks at birth; Apgar score ≥ 7 at 10 min; birth weight between 3rd and 97th percentiles; birth cranial circumference greater than 10th percentile; periventricular leukomalacia (PVL) grade 1; intraventricular haemorrhage (IVH) grade 1–2; and hypoglycaemia, hyponatraemia, and hypocalcaemia are permitted, provided they are not persistent and severe. 

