### 3.8. Randomisation

A centralised patient randomisation will be performed using a secure, web-based randomisation system, through which the study investigator of each centre can register new patients and obtain the treatment arm assignment.

A block allocation sequence with variable block sizes (block size 2–4), stratified by GA and gender, will be generated using Stata statistical software (StataCorp, College Station, TX, USA) with the “ralloc” command. In case of twins, randomisation will be conducted at the level of the family (i.e., twins will be randomised to the same group). The allocation sequence will be concealed from the investigators.

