### 8.2. Secondary Outcomes

To assess the effect of EVC on the neurobehavioral and developmental outcomes of newborns, as well as on maternal stress and presence in the NICU, the values for the different scales and questionnaires will be compared (at the time points specified in the Secondary Outcome Measures) between the intervention and control groups. Confounding variables will be entered in the analysis (i.e., familiar socio-economical score, gestational age at birth) to partial out any effect which they could have on the difference between the outcome measures. For continuous variables the Wilcoxon-Mann-Whitney test will be applied, while for categorical variables the chi-squared test (or Fisher’s exact test where appropriate) will be applied. 

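### The primary between-group HRV test ignores postmenstrual age at recording, which may vary by many weeks; the cost is precision, not validity

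*Protocol article*

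**What the plan says.** **Who is recorded, and when.** Section 3.5 admits infants with "GA between 25 + 0 and 32 + 6 weeks at birth". Section 3.9 sets the start by eligibility, not by a fixed age: "This intervention will start soon after birth, once the inclusion criteria are met, and will continue over 2 weeks during hospitalisation". The upper limit in the same section is that "participants will be excluded if they reach the inclusion criteria at more than 36 weeks of GA at test". Among the exclusions in section 3.6 is "requiring respiratory support with high flow/nCPAP", so eligibility can depend on an infant's clinical course as well as on birth date.

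**Maturity and HRV.** Section 2 says that autonomic maturation goes with rising HRV and that gestational age "correlates with HRV; preterm infants demonstrate lower HRV parameters than term infants".

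**Design and analysis.** Section 3.8 describes "A block allocation sequence with variable block sizes (block size 2–4), stratified by GA and gender". Section 5.1 plans change from baseline across the singing, speaking and control conditions. Section 8.1 uses the Friedman test within groups. Between groups it uses the Kruskal–Wallis test on HRV parameters from the first five minutes of the pre, during and post recordings, and it names no covariate. Covariates appear only in section 8.2, for secondary outcomes: "familiar socio-economical score, gestational age at birth".

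**The concern.** At the moment of an ECG recording, an infant's maturity reflects time since birth as well as gestational age at birth. The protocol recognises this when it applies its 36-week limit at test rather than at birth, but it then uses age at test only as a cut-off.

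If HRV depends on maturity, as section 2 argues, the spread in age at recording adds to the between-infant variance against which the primary comparison is judged. An unadjusted rank test leaves all of that variance in. Stratifying by gestational age removes some chance imbalance, but a test that ignores the strata does not turn this into a smaller standard error. With about 32 evaluable infants per arm, an avoidable loss of precision matters. A visible imbalance in age at test would also leave readers unsure how to interpret the primary result.

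**Working it through.** **1. Possible spread in age.** The earliest possible start is shortly after birth at 25+0 weeks and the latest is 36 weeks, so first sessions could in principle span 36 − 25 = 11 weeks. Two weeks of sessions take the last recordings to about 36 + 2 = 38 weeks. These are limits, not an expected distribution. The stated limits would allow, for illustration, an infant born at 26 weeks to start at 35 and another born at 32 weeks to start at 33.

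**2. The plan's own sample size.** Section 3.7 gives HF 15 (SD 2.6) against 17 (SD 2.4), LF 31 against 25 (SD 4.9), alpha 0.025, and 0.80, which is written as beta and read here as power. Sidedness is not stated; two-sided fits best.

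- Pooled HF SD = √((2.6² + 2.4²)/2) = 2.502.
- HF: n = 2 × (2.2414 + 0.8416)² × (2.502/2)² = 29.75, so 30 per group against 29 stated. This is close enough to count as reproduced.
- LF: n = 2 × (3.083)² × (4.9/6)² = 12.7, so 13. HF is the binding outcome.
- Evaluable after 20% loss: 40 × 0.8 = 32 per group.
- Planned effects: HF 2/2.502 = 0.80 SD; LF 6/4.9 = 1.22 SD.

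**3. What adjustment would buy.** Let r be the correlation between HRV level and postmenstrual age at recording. The documents give no value, so r is an assumption.

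- Residual variance is multiplied by 1 − r².
- Equivalent gain in infants is 1/(1 − r²) − 1.
- n per group for HF is 29.75 × (1 − r²), rounded up.
- Power for HF is Φ(2 / (2.502 × √(1 − r²) × √(2/n)) − 2.2414).

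| Assumed r | Variance removed | Equivalent gain in infants | HF n per group | HF power, 29 per group | HF power, 32 per group |
|---|---|---|---|---|---|
| 0 | 0% | 0% | 30 | 0.79 | 0.83 |
| 0.30 | 9% | 10% | 28 | 0.83 | 0.87 |
| 0.45 | 20% | 25% | 24 | 0.88 | 0.91 |
| 0.60 | 36% | 56% | 20 | 0.94 | 0.96 |

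These figures use a normal approximation for means, in line with the mean-and-SD inputs of section 3.7. They are not exact for a rank test.

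**4. Chance imbalance.** The standardised difference between arms in a covariate that is not stratified has SD √(2/32) = 0.25.

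- Its 95% range is ±1.96 × 0.25 = ±0.49 SD, and a difference beyond 0.25 SD has probability 32%.
- An imbalance at the 95% edge would move the unadjusted HRV contrast by r × 0.49 = 0.15, 0.22 and 0.29 SD at r = 0.30, 0.45 and 0.60.
- In HF units (× 2.502) that is 0.37, 0.55 and 0.74, against a target difference of 2.

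This treats age at test as wholly unstratified. Stratification by gestational age would narrow the range somewhat.

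**5. Validity of the unadjusted test.** A simulation of the Kruskal–Wallis test with 32 per group, nominal level 0.025 and postmenstrual age left out gave rejection rates under the null of 0.024, 0.027 and 0.022 at r = 0, 0.5 and 0.7. Omitting the covariate does not inflate type I error.

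**The case against.** Four points can be made for the plan, and the first three stand in whole or in part.

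- **Randomisation already protects the comparison.** Age at the first session is fixed before treatment, so it is balanced in expectation, and stratifying by gestational age helps in part. A reader might infer that the HRV comparison is biased. The documents do not support that: the shifts in step 4 are chance draws that the unadjusted standard error already allows for, and type I error holds.
- **Each infant serves as its own control.** Change from baseline (section 5.1) would remove much of the between-infant difference in maturity, because the baseline is taken at nearly the same age. This stands for an analysis of change, where the relevant correlation could be much smaller than those assumed above. However, section 8.1 describes the between-group test on window values without subtracting baseline, so the protection is not secured as written.
- **The true spread is unknown.** Sessions are meant to begin soon after birth, 36 weeks is an exclusion limit, and the other exclusions may remove some infants who stabilise late. The size of the gain therefore cannot be fixed from the documents.
- **Covariates are often left to a statistical analysis plan.** That is true in general. Here, though, section 8.1 names the primary test and section 8.2 names covariates for secondary outcomes only, so the comment addresses a stated choice.

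Two further inferences go too far. The protocol says that gestational age correlates with HRV. It does not say that age at recording is the main driver, or that gestational age at birth is a reversed proxy for it. Nor does the plan adjust the primary outcome for gestational age at birth: that covariate belongs to section 8.2. The term GA in section 3.8 is not defined there; GA at birth is the likelier reading.

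**Conclusion.** The point holds as a matter of efficiency. The protocol allows age at recording to vary by many weeks, links HRV to maturation, and then fixes a primary between-group test that uses no maturity variable at all. The cost is lost precision and exposure to chance imbalance.

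The gain of about 10% to 56% rests on assumed correlations of 0.30 to 0.60 with HRV level. It would be smaller for change from baseline, and probably smaller on top of a model that already contains baseline HRV. A reader might also infer that the sample size is wrong. It is not affected: the stated 29 per group is close to the unadjusted calculation, and nothing shows that it relied on adjustment. The change is worth making before any unblinded analysis because it costs little, but the primary result would not be invalid without it.

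**What to change.** - In section 8.1, replace the unadjusted between-group Kruskal–Wallis test with a model that can take covariates, for example ANCOVA on transformed or ranked HRV. Include postmenstrual age at the first session and the infant's own baseline HRV.
- Reconcile this with section 5.1, so that one passage states whether the primary contrast is a change from baseline or a baseline-adjusted value.
- Report postmenstrual age at the first session by arm in the baseline table.

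**Cost.** This is more than a wording change, because the Kruskal–Wallis test takes no covariate and the primary method itself must change. It brings slightly more analysis work and modelling assumptions, such as the transformation and the form of the age effect, which should be fixed in advance. No new data are needed: age at test must already be known to apply the 36-week limit.

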### 1.3. Early Protective Interventions

A number of experimental studies have found that relation-based early interventions can impact infant development, mainly if they provide high-quality and ecologically pervasive actions [34], with the main effects lasting for the first two years of life [35]. Changes in sensory inputs and mother-driven environmental enrichment at this stage can affect brain development and stress regulation. Preterm birth carries severe risk factors for a dysfunctional mother-infant interaction cycle with the potential for developing lower maternal sensitivity and responsiveness and higher maternal control [36]. Both these forms of dysfunctional regulatory patterns show a lack of synchronicity, which is an essential element in the interactive regulation between developing attachment behaviour [37]. In the regulatory process of human attachment, maternal vocalisations to infants are “biologically relevant signals” [38] and affect brain development. The mother’s external regulation of the infant’s state during particular critical periods may represent the essential factor influencing the experience-dependent growth of brain areas, eliciting high levels of metabolic energy for the tuning of the brain cortical-subcortical circuits involved in processing socioemotional information [39].

Several studies investigated the effects of the live maternal voice—namely singing mothers supported by professionals—during music therapy interventions in the NICU, primarily suggesting it as an early music intervention in the frame of environmental enrichment and infant emotional development [40]. In these studies, the maternal singing, supported by instruments and by the music therapist, has been primary used to promote parent-infant interaction [41,42], to sustain preterm infants’ regulation and vital signs [43,44], and as a strategy to involve families in the early care in the NICU [45,46,47]. 

At this stage, early maternal care can affect an infant’s ability to react and positively adapt to stressful conditions: skin-to-skin contact [48], early vocal contact [49], maternal tactile stimulation [50], and active parental closeness.

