### 3.10. Control Group

Mothers in the control group will be encouraged to spend the same amount of time next to the incubator, observing the infant’s behaviours through a standard cluster of indicators. It’s important that mothers in the control group are sustained in the presence and in the observation tasks, in order to minimize the negative effects of separation in the NICU.

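### Touch is barred, and eye contact and face position prescribed, in EVC sessions only, so an HRV difference between arms cannot be assigned to voice alone

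*Protocol article*

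**What the plan says.** Section 3.9 gives EVC mothers three instructions besides speaking and singing. They "will be asked to refrain from touching the infant, while maintaining eye contact with them". On position, they are to bring the face to the opening of the incubator, with as little distance from the infant's head as they can manage.

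The control instructions are in sections 3.2, 3.3 and 3.10. "Mothers in the control group will be encouraged to spend the same amount of time next to the incubator", where they observe the infant against a set of indicators. They do this "with the subsequent compilation of an observation grid developed ad hoc", and they "will be asked not to vocally interact with them during the observational intervention". None of these sections gives control mothers a rule on touch, eye contact or where to place the face.

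Section 5.1 measures HRV during the sessions and compares change from baseline across singing, speaking and control. Section 8.1 compares the two groups on the first five minutes of each session period (before, during and after).

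**The concern.** The protocol goes some way towards isolating the voice. It silences control mothers, bars touch in the EVC arm, and checks at every session that the voice can be heard over background noise (section 4.1.3). Barring touch in one arm only leaves that work half done.

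The protocol's own background treats the unmatched elements as active. Section 1.3 lists "maternal tactile stimulation [50], and active parental closeness" beside early vocal contact among forms of maternal care that can influence how the infant copes with stress.

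Any touch, closeness or eye contact would act while the primary endpoint is being recorded. Randomisation balances the infants, but it does not remove a difference that is written into the two session procedures. Section 7 names only contamination between groups as a potential confound.

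**Working it through.** No published figure is at issue, so the check is a comparison of the printed session rules.

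| Session element | EVC arm (3.9) | Control arm (3.2, 3.3, 3.10) | Matched? |
|---|---|---|---|
| Duration | 20 min: speaking 10, singing 10 | Same amount of time | Yes |
| Bedside presence | At the incubator or crib | Next to the incubator | Yes |
| Visual attention | Observes the infant's reactions | Observes the infant's behaviour | Broadly |
| Voice | Speaks and sings | Vocal interaction barred | No, by design |
| Touch | Barred | No rule printed | No |
| Eye contact | To be maintained | No rule printed | No |
| Face position | At the opening, close to the head | No rule printed | No |

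To see what this does to the contrast, assume for simplicity that effects add. Let

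- *v* be the effect of voice on an HRV parameter during a session;
- *f* be the effect of the EVC face position and eye contact beyond what control mothers happen to do;
- *p* be the share of control sessions in which the mother touches the infant;
- *δ* be the average effect of such touch on the parameter.

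The EVC mean moves by *v* + *f* and the control mean by *pδ*. The arm difference is therefore

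D = *v* + *f* − *pδ*.

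Three results follow.

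1. With the printed rules, only the sum D is estimated. If *δ* has the sign of the expected EVC effect, touch narrows the difference. If it has the opposite sign, touch widens it.
2. If touch is barred in both arms and the rule is kept, *p* = 0 and D = *v* + *f*, the effect of the face-to-face EVC package.
3. If position and eye contact are matched as well, *f* = 0 and D = *v*, the effect of voice.

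For scale, section 3.7 plans on HF power moving from 15 to 17 (17 − 15 = 2) and LF power from 31 to 25 (25 − 31 = −6), in the units printed there. The documents give no value for *p*, *δ* or *f*, so the distortion cannot be expressed as a share of these effects.

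The comparison of singing with speaking inside the EVC arm is not affected, because both are delivered under the same position, eye-contact and touch rules.

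**The case against.** The strongest reply has three parts.

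**The article is a condensation.** Section 3.10 is two sentences long, and a fuller manual may bar touch in control sessions. This stands in part: silence is not permission. A reader might infer that control mothers will touch their infants, or may sit away and look elsewhere. The documents do not support that. Section 3.3 asks these mothers to watch spontaneous behaviour, which fits poorly with touching and rules out looking away throughout. Still, the article prints session rules for both arms, down to when the grid is filled in and the bar on vocalising. The touch rule appears for one arm only, and that is a mismatch in what is printed.

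**EVC is more than sound.** Sections 1.4 and 2 describe it as relational and interactive as well as auditory, so eye contact and face position can be read as part of how it is delivered. Matching them in the control arm would change the comparator, which is a legitimate choice either way. This stands, and it is why matching is offered as one of two options for those elements. It does not cover touch, which is excluded from the EVC package itself. Section 2 also attributes expected effects to auditory enrichment and linguistic exposure, and those attributions need the voice to be separable or the claim to be worded more narrowly.

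**Much is already matched.** Time, presence and observation are common to both arms. This is correct, and the confounding is only partial.

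A reader might also infer that medical procedures are allowed during control sessions, because the ban stands in section 3.9. The text does not show this. Section 3.3 also calls the control session an intervention, and it sets the gap between medical exams and recording sessions without limiting it to one arm.

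**Conclusion.** The point holds in a limited form. Touch is controlled in EVC sessions and left open in control sessions while the primary outcome is recorded. Eye contact and face position are prescribed in the EVC arm only. An arm difference in HRV therefore cannot be assigned to voice alone.

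Its size is unknown. Touch in control sessions is possible but not shown, and the direction of its effect on HRV is not given. The conclusion rests on reading the printed instructions as those the sites follow; a fuller control manual with the same touch rule would settle that part.

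It would go too far to say that the trial cannot be interpreted. Comparing the EVC package with quiet observation is a valid randomised contrast, and it becomes cleaner once touch is handled alike. The change is worth making because it protects the primary contrast at almost no cost.

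**What to change.** 1. In section 3.10, apply to control mothers the same no-touch session rule that section 3.9 sets for EVC mothers.
2. Use the session video to flag touch in either arm as a deviation. Section 3.9 describes the cameras under the intervention, while section 5.1 relies on recorded sessions for scoring behavioural state. The text should confirm that control sessions are filmed in the same way and that the view is wide enough to show touch.
3. For eye contact and face position, choose one of two courses and write it down. Either give control mothers the same instructions, with the grid still completed afterwards, or state in sections 1.5 and 2 that the estimated effect is that of face-to-face EVC against quiet observation, not of voice alone.

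The cost is a few sentences in the protocol and training sheet, plus one extra item when the video is coded. No further infants or visits are needed. The downside is a slightly more prescriptive control session. If position and eye contact are matched, the comparator also becomes silent face-to-face contact, which is a different question and should be chosen deliberately.
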